**6.3 Dose modifications due to non-hematologic toxicity**

If the non-hematological toxicity is not clearly related to a certain investigational drug, consider adjusting the dose of all drugs that may cause the adverse reactions; if the non-hematological toxicity is clearly related to a certain investigational drug, consider only adjusting the dose of this drug, while the dose of other investigational drugs may not be adjusted.

Dose adjustment for the first occurrence of non-hematological toxicity:

- Diarrhea
- If diarrhea occurs at any time, the patient must recover to less than Grade 1 diarrhea before restarting treatment. For Grade 1 diarrhea, administer the investigational drug at the original dose; for Grade 2 diarrhea, administer irinotecan and 5-FU at 85% of the original dose; after a dose reduction, if the same or higher grade of toxicity recurs, further reduce irinotecan and 5-FU to 75% of the original dose. For Grade 3 diarrhea, administer irinotecan and 5-FU at 75% of the original dose; after dose reduction, if the same or higher grade of toxicity recurs, further reduce irinotecan and 5-FU to 60% of the original dose. If the patient presents with the following conditions, including Grade 4 diarrhea, diarrhea with fever, and diarrhea with Grade 3 to 4 granulocytopenia, administer irinotecan and 5-FU at 60% of the original dose. After dose reduction, discontinue the treatment if the same or higher grade of toxicity recurs.
- Bilirubin increased

Once bilirubin increased occurs, it is recommended to rule out bilirubin increased caused by biliary obstruction and tumor progression. If bilirubin is > 1.5 × ULN, irinotecan is no longer recommended.

- Transaminases increased

In this study, if the transaminases level is abnormal, it is recommended to rule out transaminase increased caused by tumor progression. Drug treatment will be withheld until toxicity recovers to baseline or ≤ Grade 1 before treatment can be restarted. For Grade 1 and 2 transaminases increased, no dose adjustment is made; for Grade 3 transaminase increased, adjust the dose of oxaliplatin/irinotecan to 80% of the original dose. For Grade 4 transaminases increased, discontinue all treatment. Once a dose reduction has been made due to hepatic function, no further dose reduction is recommended if no worsening of indicators is observed.

- Stomatitis

If stomatitis occurs at any time, the patient must recover to less than Grade 1 stomatitis before restarting treatment. Dose reduction is required as follows: for Grade 1 stomatitis, administer the investigational drug at the original dose; for Grade 2 stomatitis, administer 5-FU at 85% of the original dose; for Grade 3 stomatitis, administer 5-FU at 70% of the original dose; for Grade 4 stomatitis, discontinue all treatment.

- Cardiotoxicity

Once angina pectoris or myocardial infarction occurs, discontinue 5-FU treatment permanently.

- Hand-foot syndrome:

For Grade 3 or 4 toxicity, withhold the drug treatment until the toxicity recovers to Grade ≤ 1 before restarting the treatment. Dose reduction is required as follows: for Grade 3 hand-foot syndrome, administer 5-FU at 75% of the original dose; for Grade 4 hand-foot syndrome, administer 5-FU at 60% of the original dose.

- Neurotoxicity

For Grade 3 or 4 neurotoxicity, withhold the drug treatment until the neurotoxicity recovers to Grade ≤ 1 before restarting the treatment. Dose reduction is required as follows: for Grade 2 neurotoxicity, administer oxaliplatin at 85% of the original dose; for patients with Grade 3/4 neurotoxicity, discontinue oxaliplatin treatment and patients in the cetuximab plus FOLFOXIRI group may continue to receive either cetuximab or FU/CF chemotherapy.

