**6.5 Management of other toxicities**

If other Grade < 3 toxicities not listed above occur, give symptomatic treatment whenever possible. If Grade 3 toxicity occurs, withhold the drug treatment. When the toxicity recovers from Grade 3 to Grade ≤ 1, administer the corresponding investigational drug at 85% of the original dose in the next treatment cycle. If Grade 4 toxicity occurs, discontinue all drug treatment. If the toxicity still does not resolve to Grade ≤ 1 four weeks after the start of the next scheduled cycle, the patient should withdraw from the treatment and be followed up according to the protocol until the toxicity is resolved.

However, in the event of certain Grade ≥ 3 adverse events (e.g., when a patient develops symptoms of fatigue, sexual function changes, and clinically insignificant dry skin), the investigator may also decide to allow the patient to continue treatment.

For the second occurrence of non-hematological toxicity, the following dose adjustment methods should be used:

If the patient experiences Grade 3 toxicity again, although the dose of the investigational drug has been previously adjusted, the study dose can still be adjusted again if the investigator believes that the treatment is in the best interest of the patient (otherwise the treatment should be stopped). Adjust the second dose to 70% of the original dose. However, for the second occurrence of Grade 4 toxicity, the above principles do not apply, and the patient should discontinue treatment in this case. If the dose has already been reduced, it cannot be increased thereafter.

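### Diarrhea dosing in Protocol 6.3: after a Grade 2 reduction, a Grade 4 or complicated episode meets both the 75% and the 60% rule, and neither is given precedence

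*Protocol*

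**What the plan says.** Protocol section 6.3 introduces its rules with "Dose adjustment for the first occurrence of non-hematological toxicity". The diarrhea bullet then sets three tracks, all as percentages of the original irinotecan and 5-FU dose:

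- **Grade 2:** 85%. On recurrence, "after a dose reduction, if the same or higher grade of toxicity recurs, further reduce irinotecan and 5-FU to 75% of the original dose".
- **Grade 3:** 75%. On recurrence, "after dose reduction, if the same or higher grade of toxicity recurs, further reduce irinotecan and 5-FU to 60% of the original dose".
- **Grade 4 or complicated:** the rule reads "including Grade 4 diarrhea, diarrhea with fever, and diarrhea with Grade 3 to 4 granulocytopenia, administer irinotecan and 5-FU at 60% of the original dose". This is followed by "After dose reduction, discontinue the treatment if the same or higher grade of toxicity recurs".

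Before any restart, "the patient must recover to less than Grade 1 diarrhea before restarting treatment".

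Section 6.5, titled for other toxicities, contains a further rule: "For the second occurrence of non-hematological toxicity, the following dose adjustment methods should be used". For a repeat Grade 3 event it allows another adjustment if the investigator judges continued treatment to be in the patient's interest: "Adjust the second dose to 70% of the original dose".

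**The concern.** The recurrence step on the Grade 2 track is triggered by the same grade or any higher one, so its words include Grade 4. The 60% sentence is triggered by the event itself and does not exclude patients who have already been reduced. Where both triggers are met, the protocol states two different doses for the same patient.

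The literal 75% reading gives a perverse result. A patient who worsened to Grade 4 despite a reduction would restart on a higher dose than a patient whose first episode was Grade 4.

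A second difficulty lies between sections. The 6.3 rules stand under a first-occurrence heading but include recurrence steps, while 6.5 offers a second-occurrence rule worded for non-hematological toxicity in general. For repeat Grade 3 diarrhea the two give different percentages, if 6.5 reaches diarrhea at all.

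The stake is patient safety and uniform dosing across the sites of a multicentre trial. The background section cites Grade 3/4 diarrhea in 25% and agranulocytosis in 40% with cetuximab plus triplet chemotherapy, so severe events of this kind are foreseeable.

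**Working it through.** No design figure is involved. The check reads each clause literally, lists which are met for each sequence, and converts the percentages to doses.

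**Clauses met, as % of the original dose.** Complicated means with fever or Grade 3-4 granulocytopenia.

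| Earlier reduction for | New event | Recurrence step | Sentence naming the event | Result |
|---|---|---|---|---|
| Grade 2 | Grade 3, uncomplicated | 75 | 75 | agree |
| Grade 2 | Grade 4 | 75 | 60 | **differ** |
| Grade 2 | Grade 2 or 3, complicated | 75 | 60 | **differ** |
| Grade 2 | Grade 1, complicated | not triggered | 60 | one answer |
| Grade 3 | Grade 4 | 60 | 60 | agree |

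The overlap is therefore confined to patients first reduced for Grade 2 diarrhea who then have Grade 4 diarrhea, or complicated diarrhea of Grade 2 or 3.

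**Does the bullet imply a rule of precedence?** Two uncomplicated repeats test this. For Grade 2 after Grade 2, the sentence naming the event gives 85% and the recurrence step gives 75%; the recurrence step must govern. For Grade 3 after Grade 3, the figures are 75% and 60%, and again the recurrence step must govern. So the sentence naming the event does not win everywhere in the bullet. Using the lowest applicable dose would fit every case, but the protocol does not say so.

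**Section 6.5.** For repeat Grade 3 diarrhea, 6.3 gives 60% and 6.5, if it applies, gives 70%. The 6.5 rule otherwise covers a second Grade 4 event (discontinue). It does not address a first Grade 4 event after a Grade 2 reduction, so it does not settle the main overlap.

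**Doses.** Starting doses come from section 5.2: irinotecan 130 mg/m2, with 150 or 100 possible under the 3+3 rule; infusional 5-FU 2400 mg/m2 in both arms; 5-FU bolus 400 mg/m2 in the doublet arm only. Restart dose = starting dose × percentage.

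| Drug (mg/m2) | 75% | 70% | 60% |
|---|---|---|---|
| Irinotecan 150 | 112.5 | 105 | 90 |
| Irinotecan 130 | 97.5 | 91 | 78 |
| Irinotecan 100 | 75 | 70 | 60 |
| 5-FU infusion 2400 | 1800 | 1680 | 1440 |
| 5-FU bolus 400 | 300 | 280 | 240 |

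Ratios: 0.75 / 0.60 = 1.25 for the overlap within 6.3; 0.70 / 0.60 = 1.17 for the possible clash with 6.5.

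**The case against.** The strongest reply is that this is a general step beside a specific rule, not a contradiction. The bullet climbs by severity, and its last dosing sentence names Grade 4 and the complications without any condition on earlier dosing. On ordinary reading that sentence governs. Reading the 75% step without context is also selective: the closing sentence on discontinuation is equally unrestricted in its words, and taken literally it would override the 75% and 60% recurrence steps, yet everyone reads it as belonging to the 60% track. Section 6.2 likewise sets a general recurrence step next to a specific Grade 4 sentence without ranking them.

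Most of this stands as a statement of intent: 60% is evidently meant, and a careful investigator would probably use it. It does not remove the overlap. The 75% step is specific too, since it is written for a patient already reduced for Grade 2 diarrhea, and in the two uncomplicated repeats the step tied to dosing history is the one that prevails. Sites must infer the precedence.

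The objection to the 6.5 point has more force. That section opens with toxicities not listed earlier, diarrhea is listed earlier, and the 70% rule is permissive. But the rule's own wording mirrors the 6.3 heading and covers non-hematological toxicity generally, so this clash is possible, not certain.

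The practical limits are also real. Recovery from diarrhea is required before restart, section 9.4 lets the investigator stop treatment, and the protocol gives no frequency for these sequences.

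**Conclusion.** The point holds as a minor inconsistency. Section 6.3 as written assigns both 75% and 60% to Grade 4 diarrhea, and to complicated Grade 2-3 diarrhea, that follows a Grade 2 reduction, and nothing in sections 6.1 to 6.5 ranks the two. Choosing the wrong clause would raise the restart dose by 25% relative to the evident intent. The 70% against 60% difference with 6.5 is a possible second clash, conditional on that rule reaching diarrhea.

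The conclusion rests on the wording alone. How many patients would be affected cannot be estimated from the protocol. ORR, sample size and error rates are not touched.

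**What to change.** Amend the diarrhea bullet in 6.3 and add one cross-reference:

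1. Limit the 75% recurrence step after a Grade 2 reduction to Grade 2-3 diarrhea without fever and without Grade 3-4 granulocytopenia.
2. State that the first event meeting the Grade 4, fever or granulocytopenia conditions takes 60%, including in patients already reduced to 85% or 75%.
3. Keep discontinuation if such an event recurs once the patient is already at 60%.
4. State that the diarrhea recurrence rules in 6.3 take precedence over the second-occurrence rule in 6.5.

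The cost is a few sentences in the next protocol amendment, with no change to design or analysis.

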**6.4** **Management of adverse reactions due to cetuximab**

- Infusion-related reactions, including anaphylaxis

Severe infusion-related reactions, including anaphylaxis, can occur frequently and in some cases can be fatal. Once severe infusion reactions occur, discontinue the drug immediately and permanently and provide emergency treatment. Some of these reactions may be reported as anaphylaxis, anaphylactoid reactions or presented as cytokine release syndrome (CRS). Symptoms may occur during the first infusion and hours after the end of the infusion or in subsequent instillations. The physician is recommended to inform the patient of the possibility of delayed onset of this reaction and ask the patient to contact the physician immediately if symptoms occur. Possible symptoms include bronchospasm, urticaria, high or low blood pressure, loss of consciousness, or shock. Angina pectoris, myocardial infarction, or sudden cardiac arrest are rare.

Anaphylaxis may occur within minutes of the first infusion, e.g., caused by preformed IgE antibodies that cross-react with the drug. These reactions are usually accompanied by bronchospasm and urticaria. These reactions may occur despite premedication. Patients who are allergic to red meat or tick bites or who are positive for IgE antibodies to cetuximab (α-1-3-galactose) have much higher risk of anaphylaxis. For these patients, the risks and benefits, including alternative therapies, should be carefully assessed before application of the drug, and the drug can only be used under the close supervision of trained professionals equipped with resuscitation equipment.

The first dose should be administered slowly, the instillation rate should not exceed 5 mg/min, and all vital signs should be closely monitored for at least 2 hours. If an infusion-related reaction occurs within 15 minutes of the first dose, the instillation should be discontinued. Careful risk-benefit assessment should be performed before subsequent infusions, including consideration of whether the patient has preformed IgE antibodies.

If infusion-related reactions occur late in the instillation or in the subsequent instillations, the corresponding management depends on the severity of the reaction:

1. Grade 1: perform instillation continuously and slowly under close monitoring
2. Grade 2: perform instillation continuously and slowly and adopt symptomatic treatment immediately
3. Grade 3 and 4: stop the instillation immediately, perform active symptomatic treatment and stop further treatment with the drug.

CRS usually occurs within 1 hour after instillation of the drug, and generally is not accompanied by bronchospasm and urticaria. CRS is usually the most serious adverse reaction of the first instillation of the drug.

Mild and moderate infusion reactions are very common and include symptoms such as fever, chills, dizziness, or dyspnea, and occur primarily during the first infusion. If the patient develops mild to moderate relevant reactions, the instillation rate of the drug should be slowed down. It is recommended to take the adjusted rate during all subsequent instillation processes.

Patients should be closely monitored, especially during the first dose. It is recommended that special attention should be paid to patients with low performance status or concomitant cardiopulmonary disease.

- Skin reactions

The main adverse reaction of the drug is skin reactions. Severe skin reactions nay occur, especially when the drug is combined with chemotherapy. The increased risk of secondary infections, primarily bacterial, can lead to complications such as staphylococcal scalded skin syndrome, necrotizing fasciitis, and sepsis, which in some cases have been reported to be fatal.

Skin reactions are very common and treatment with the drug should be interrupted or discontinued when they occur. Clinical practice guidelines recommend prophylactic treatment with oral tetracycline (6-8 weeks) and 1% hydrocortisone topical cream with moisturizers. Moderate to high potency corticosteroids or oral tetracycline antibiotics have been used in the treatment of skin reactions.

For patients who develop intolerable severe (≥ Grade 3; Common Terminology Criteria for Adverse Events, NCI-CTCAE) skin reactions, treatment with the drug must be interrupted. Treatment should only be restarted when the reactions have resolved to Grade 2 (see National Cancer Institute website for detailed CTCAE grading classifications). If the severe skin reaction occurs for the first time, no dose adjustment of the drug is required.

If the severe skin reaction occurs for the second or third time, the use of the drug must be interrupted again.

Resume treatment at a lower dose only if the reaction has resolved to Grade 2 (for the second occurrence: 200 mg/m^2^ by body surface area; for the third occurrence: 150 mg/m^2^ by body surface area).

If the severe skin reaction occurs for the fourth time, or the skin reactions cannot be resolved to Grade 2 after treatment interruption, the treatment with the drug should be discontinued permanently.

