12. Patients who have completed the treatment specified in the protocol or have not completed the treatment due to intolerable toxicity, but have not experienced tumor progression, are followed up every 3 months, including physical examination and imaging examination until tumor progression. For patients with tumor progression, follow-up will be performed by phone every 3 months until death. The following information should be collected as much as possible during follow-up: subsequent anti-tumor treatment and survival data. Patients with preoperative disease progression should withdraw from the study and enter the follow-up period as well.

Flowchart:

Technically resectable but ≥ 5 metastatic lesions or technically unresectable

Randomization

Cetuximab plus FOLFOXIRI

Cetuximab plus FOLFOX

Chemotherapy: 6 to 8 courses (3 to 4 months)

Resectable

Progression

Disease controlled but remains unresectable

Switch to other therapy or maintenance therapy

Surgical resection

Continue chemotherapy: 4 to 8 courses (2 to 3 months)

Switch to other therapy

Progression

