**Cetuximab + mFOLFOX6 regimen**

Cetuximab 500 mg/m^2^ ivd 90 min d1

Oxaliplatin 85 mg/m^2^ ivd 3h d1

L-leucovorin 200 mg/m^2^ ivd 2h d1 (d,l-leucovorin 400 mg/m^2^)

5-FU 400 mg/m^2^ iv d1

5-FU 2400 mg/m^2^ ivd civ 46h d1

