**Cetuximab + mFOLFOXIRI regimen**

Cetuximab 500 mg/m^2^ ivd 90 min d1

Irinotecan 130 mg/m2 ivd d1 (The starting dose of irinotecan is 130 mg/m2, according to the “3 + 3” design. If 0/3 patients experience dose limiting toxicity (DLT), the dose should be increased to 150 mg/m2; if 1/3 patients experiences DLT, the number of enrolled patients should be increased to 6; if ≤ 1/6 patients experience DLT, the dose should be increased to 150 mg/m2; if ≥ 2/6 patients experience DLT, the dose of irinotecan should be decreased to 100 mg/m2.

At the dose of 150 mg/m2, if 0/3 patients experience DLT, the dose is determined to be 150 mg/m2; if 1/3 patients experiences DLT, the number of enrolled patients should be increased to 6; if ≤ 1/6 patients experience DLT, the dose is determined to be 150 mg/m2; and if ≥ 2/6 experience DLT, the dose is determined to be 130 mg/m2). UGT gene detection is recommended. For patients with UGT*28 7/7, UGT*6 A/A, UGT*28 6/7 and UGT*6 A/G, irinotecan at the dose of 130 mg/m2 is used, no need for escalation)

Oxaliplatin 85 mg/m^2^ ivd 3h d1

L-leucovorin 200 mg/m^2^ ivd d1 (d,l-leucovorin 400 mg/m^2^)

5-FU 2400 mg/m^2^ ivd civ 46h d1

The above regimen is repeated every 14 days.

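### First cetuximab dose: the 90-minute infusion in Section 5.2 cannot be given within the 5 mg/min first-dose limit in Section 6.4 at any body surface area above 0.9 m²

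*Protocol*

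**What the plan says.** Protocol Section 5.2 gives the same cetuximab line in the mFOLFOX6 and the mFOLFOXIRI regimen: "Cetuximab 500 mg/m^2^ ivd 90 min d1". The listing ends with "The above regimen is repeated every 14 days", and neither regimen sets a different time or rate for the first infusion.

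Section 6.4 has a rule for the first dose alone: "The first dose should be administered slowly, the instillation rate should not exceed 5 mg/min". The same section explains why the first dose is treated with care. It says "Severe infusion-related reactions, including anaphylaxis, can occur frequently and in some cases can be fatal", and of cytokine release syndrome it says "CRS is usually the most serious adverse reaction of the first instillation of the drug". For patients whose infusion was slowed because of a mild or moderate reaction, it adds "It is recommended to take the adjusted rate during all subsequent instillation processes".

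On the number of courses, the text of Sections 5.1 and 5.2 allows at most 12 courses in total before and after surgery. The flowchart in Section 5.1 shows "Chemotherapy: 6 to 8 courses (3 to 4 months") for the conversion phase and, in a later box, "Continue chemotherapy: 4 to 8 courses (2 to 3 months").

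**The concern.** For the first dose, Section 5.2 fixes a duration and Section 6.4 fixes a maximum rate. The dose is set per m², so the two can agree only below some body size. If that size is smaller than any adult in the trial, every first infusion must depart from one of the two instructions.

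The limit applies to the infusion for which the protocol itself expects the most serious reactions. Treatment orders are likely to be prepared from the regimen listing. A site that does this as written would exceed the protocol's own safety limit at cycle 1, in both arms. Later doses are not in conflict, because the limit is written for the first dose only.

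A smaller matter of the same kind is the later flowchart box. Its upper limit of 8 courses looks too long for its own label of 2 to 3 months, and too many for the 12-course total.

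**Working it through.** **Inputs**

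- Dose 500 mg/m² and infusion time 90 min: Section 5.2, both regimens.
- First-dose limit 5 mg/min: Section 6.4.
- Course length 14 days: Section 5.2.
- Course total 12: Sections 5.1 and 5.2.
- Flowchart ranges of 6–8 and 4–8 courses: Section 5.1.
- BSA: not given in the protocol. Eligibility is age 18 to 70 (Section 3.1), and I assume 1.2 to 2.2 m².

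**When does 90 minutes agree with the limit?**

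- Maximum dose in 90 min at the limit: 5 × 90 = 450 mg.
- BSA for which this is the full dose: 450 / 500 = 0.9 m².

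This threshold uses only the protocol's figures. The stated 90 minutes is reproduced at 0.9 m² and is too short above it.

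**Size of the excess**

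Rate over 90 min = 500 × BSA / 90. Time needed at the limit = 500 × BSA / 5 = 100 min per m².

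| BSA (m²) | Dose (mg) | Rate over 90 min (mg/min) | Rate / limit | Time at limit (min) | Beyond 90 min |
|---|---|---|---|---|---|
| 0.9 | 450 | 5.0 | 1.0 | 90 | 0 |
| 1.2 | 600 | 6.7 | 1.3 | 120 | 30 |
| 1.4 | 700 | 7.8 | 1.6 | 140 | 50 |
| 1.7 | 850 | 9.4 | 1.9 | 170 | 80 |
| 2.2 | 1100 | 12.2 | 2.4 | 220 | 130 |

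**Flowchart: duration (minor)**

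Days = courses × 14; months = days / 30.4.

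- 4 courses: 56 days, 1.8 months.
- 6 courses: 84 days, 2.8 months.
- 8 courses: 112 days, 3.7 months.

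So 4 to 6 courses fit the label of 2 to 3 months and 8 do not. The conversion box in the same chart gives up to 4 months for 8 courses, which is right.

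**Flowchart: course total (minor)**

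This part assumes that the later box follows resection. Crossing 6, 7 or 8 conversion courses with 4, 5, 6, 7 or 8 further courses gives 3 × 5 = 15 combinations. Six stay within 12 (6+4, 6+5, 6+6, 7+4, 7+5, 8+4) and nine exceed it, up to 8 + 8 = 16. After the recommended 8 conversion courses, only 12 − 8 = 4 more fit.

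**The case against.** The strongest reply is that a specific rule overrides a general one. Section 5.2 is a one-line listing for all cycles, while Section 6.4 is written for the first dose only. Someone who reads both can run the first dose at 5 mg/min or slower and later doses over 90 minutes. On that reading only a cross-reference is missing. The reading is possible and may be what was intended. But Section 5.2 makes no exception and does not point to Section 6.4, and Section 6.4 sits under management of adverse reactions, where a dosing instruction is easily missed. A safety limit on every patient's first infusion should not rest on each site working out which section prevails.

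The protocol also has other first-dose safeguards: at least 2 hours of vital-sign monitoring, stopping for a reaction within 15 minutes, and routine diphenhydramine beforehand (Section 6.6). These lower the risk but do not remove the rate conflict, and Section 6.4 notes that anaphylaxis may occur despite premedication. It is fair to add that the protocol gives no data on how reaction risk changes between 5 and 12.2 mg/min, so the clinical harm cannot be sized.

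The cetuximab line is the same in both arms, so the conflict itself builds in no difference between them. That is accepted; the point concerns dosing and safety.

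On the flowchart, the arrows are missing from the text I worked from, and placing the later box after surgery is inferred from its order. The 12-course total in the text can also be taken to govern, and combinations such as 6+6, 7+5 and 8+4 respect it. These cautions stand for the course total. The mismatch between 8 courses and 2 to 3 months does not depend on where the box sits.

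**Conclusion.** The concern holds. At any BSA above 0.9 m², the Section 5.2 infusion time and the Section 6.4 first-dose limit cannot both be met, and nothing in the protocol reconciles them. That covers essentially every eligible adult in both arms. The threshold is exact; the excess of 1.3 to 2.4 times the limit rests on the assumed BSA range of 1.2 to 2.2 m². The conflict is confined to the first dose and does not touch the sample size or the primary analysis. It should be fixed because, followed as written, the regimen line breaks the protocol's own safety limit.

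The flowchart point is minor. The duration label is wrong at its upper end whatever the layout; the overshoot of the 12-course total depends on the inferred position of the box.

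**What to change.** In both Section 5.2 regimens, replace the single infusion time with wording such as: *First dose: no faster than 5 mg/min (about 100 min per m² of BSA). From the second dose: 90 min if the first was tolerated; if the rate was slowed for a reaction, keep the slowed rate (Section 6.4).* The last clause is slightly firmer than Section 6.4, which only recommends keeping the adjusted rate; the sponsor can retain the softer form without affecting the main correction.

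In the flowchart, change the later box to *4 to 6 courses (2 to 3 months), total before and after surgery not to exceed 12*.

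The cost is one short clarifying amendment and a memo to sites. Each patient has one longer first infusion, by about 30 to 130 minutes at a BSA of 1.2 to 2.2 m², which Section 6.4 already requires.
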